##### **1) Time series and SMR approaches**

The study population will be the adult population of all practices with continuous follow-up from 1st March 2014 and with last data collection dates no more than 2 months before the date of the most recent CPRD build ("time-series cohort").

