### I. Feasibility counts

Counts based on April 2020 builds

|                                                                      | CPRD GOLD                               | CPRD Aurum            |
|----------------------------------------------------------------------|-----------------------------------------|-----------------------|
| Alive and registered with up to standard* practice on 1 January 2020 | 3 152 150                               | 11 090 586            |
| UK countries represented                                             | All                                     | England and N Ireland |
| English regions represented                                          | All except North East and East Midlands | All                   |
| Median (IQR) weekly deaths in 2019                                   | 560 (537-620)                           | 1657 (1549-1845)      |
| January 2019 deaths                                                  | 3066                                    | 8563                  |
| January 2020 deaths                                                  | 2747                                    | 8318                  |
| February 2020 deaths                                                 | 2115                                    | 6613                  |

\*Up to standard date only available in CPRD GOLD

[figure not shown]

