#### J. Sample size considerations

We will use all available data in CPRD GOLD and CPRD Aurum to maximise regional coverage and the number and combination of comorbidities that we can study whilst modelling changes on a weekly basis. Data extraction will be minimised by using the CPRD GOLD Define and Refine tools to ascertain covariates of interest only, rather than extracting full clinical data (as discussed with [name] and [name]).

Methods for computing sample size and power are not well developed for time series analysis, so we took an empirical approach by combining recent CPRD GOLD denominator data with a simulated pandemic starting in week 9 of the final year which doubles death rates and affects patients with a given comorbidity (simulated to have similar prevalence to cancer) twice as badly. Using the time series approach, the IRR (95% CI) for the pandemic was 1.89 (1.74-2.07) and the comorbidity interaction (1.97, 1.85-2.08). The confidence intervals included the true values (2.0 and 2.0) with adequate precision. We therefore expect the coverage to be good with this study size, even when estimating interaction terms. 8% of cells had zero denominators in the weekly time series dataset created from these simulated data, necessitating some collapsing of strata, and this would rise further if stratifying by >1 comorbidity, hence the need for maximum data (using both GOLD and Aurum) to enable us to explore joint associations of combinations of covariates, using mutually adjusted models.

We will use the July 2020 build for the initial primary care only analyses because these data are the most timely and updated monthly. Our study period will end on 30 April 2020 as there appears to be a two-month delay in registering deaths in primary care data. Analyses will be updated monthly.

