#### **N. Exposures, Outcomes and Covariates**

The main exposure of interest is the Covid-19 pandemic starting from 1st March 2020.

The main outcome is mortality, identified from primary care data using the CPRD derived death date. In secondary analyses we will use updated linked ONS mortality data when available to repeat the analysis using the ONS death date.

Covariates of interest for stratification are:

- Geographical region
- Age (initial time series counts to be generated in 5 year categories, then collapsed further for analysis)
- Sex
- Smoking status (current, never, ex)
- BMI group (WHO groupings)
- Ethnicity (White, South Asian, Black, Mixed Other)
- Number of individuals in a household (CPRD GOLD only)
- Care home residency (CPRD GOLD only)
- History of comorbidities including those relevant to government “vulnerable groups” policy\*:
  - o Asthma
  - o Chronic respiratory disease (other than asthma)
  - o Cardiovascular disease
  - o Diabetes
  - o Cancer
  - o Chronic liver disease
  - o Chronic neurological diseases
  - o Chronic kidney disease
  - o Organ transplant recipients
  - o Problems with spleen
  - o On immunosuppressive drugs
  - o Hypertension
  - o Autoimmune disease
  - o Endocrine disease (including thyroid others)
  - o Multimorbidity

We will use code lists and definitions developed by the LSHTM Health Protection Research Unit on Immunisation where available, and where needed develop new code lists using systematic dictionary keyword searches, manual review, and clinical sign-off; these will be published online and linked in research outputs.

\*Current UK government guidance on who should be considered vulnerable has been largely based on policies developed for previous epidemic respiratory viruses, notably influenza. Understanding of Covid-19 risk factors is improving rapidly. We will submit a protocol amendment should new Covid-19 risk factors that can be measured using the available data emerge during the study.

[figure not shown]

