## O. Data/ Statistical Analysis

To ensure our conclusions are robust, several approaches will be taken (with different strengths and limitations). We would expect the overall patterns and conclusions of the analyses to be similar. Any discrepancies in the patterns or results will be investigated and reported. In each case we will use data up to two months before the CPRD build date (i.e. data to end April 2020, from the build released in early July 2020) and analyses will be updated monthly.

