**T. Limitations of the study design, data sources, and analytic methods**

**Data sources**

Our initial analyses will use primary care data only. This is the mostly timely data available to us as it is updated monthly and we believe that deaths are recorded within two months. Small lags have been reported between the date of death in primary care records compared to death registration data. We will therefore validate our approach through comparison with nationally reported excess mortality data.

Measurement of covariates such as ethnicity and conditions treated in hospital will also be affected. We will acknowledge these limitations and repeat our analyses using linked HES APC and mortality data when available.

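### Practice eligibility and study end are both set two months before the build, so practices near the limit do not get the two months the plan allows for late-recorded deaths

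*Protocol*

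**What the plan says.** Section J gives both the end date and its reason: "Our study period will end on 30 April 2020 as there appears to be a two-month delay in registering deaths in primary care data". The data source is fixed in the same section: "We will use the July 2020 build for the initial primary care only analyses". Section O turns this into a general rule, "In each case we will use data up to two months before the CPRD build date", with the example of an early July build giving data to the end of April. Section T repeats the premise: "we believe that deaths are recorded within two months".

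Section L, for the time series and SMR approaches, admits adult patients of practices followed continuously from 1 March 2014 and "with last data collection dates no more than 2 months before the date of the most recent CPRD build".

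Three other statements matter. Section N starts the exposure on 1 March 2020 and takes the outcome from the CPRD derived death date. Section O counts everyone under active follow-up in the weekly denominator. Sections J and O say that the analyses are updated monthly, so the rule rolls forward with each build.

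**The concern.** A death can enter the data only if the practice has recorded it by its last collection. The time available for recording therefore runs from the death to that collection, not to the build. The plan measures its two-month allowance from the build and also lets the last collection fall up to two months before the build. For a practice at that limit, the whole allowance is used up.

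The error does not cancel between periods. For a practice last collected on 1 May 2020, every day up to 29 February has at least two months for recording, and almost every day from 1 March has less. Incomplete recording then coincides with the exposure indicator. The people whose deaths are unrecorded still count as person-time, so the pandemic-period rate is too low. Estimated excess mortality moves towards no excess, in results that Section S intends to release early to inform policy.

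**Working it through.** **Inputs.** From the protocol: build in early July 2020 (Sections J and O), taken as 1-7 July; cut-off and eligibility limit both at build minus two months (Sections O and L); pandemic window 1 March to 30 April 2020, which is 31 + 30 = 61 days; intended allowance of two months, taken as 61 days (30 April to 30 June). The protocol gives neither the spread of last collection dates nor the distribution of recording delays, so steps 4 and 5 rest on assumptions.

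**1. The plan's own date.** A build on 1-7 July minus two months is 1-7 May. This agrees with data to 30 April.

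**2. Earliest eligible last collection.** The same subtraction gives 1-7 May. That is 1-7 days after the study end, against the 61 intended.

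**3. Pandemic days with the full allowance.** A practice last collected on 1 May has 61 days or more only for deaths on 1 March: 1 of 61 days. For 7 May it is 7 of 61, and for 1 June 32 of 61. All 61 days are covered only from 30 June.

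**4. Share of pandemic-window deaths captured.** Let g be the days from death to last collection, with deaths spread evenly over the window. Two assumed delays are used:
- uniform over 0-61 days: captured share = min(g/61, 1);
- exponential with 95% recorded by day 61: captured share = 1 - exp(-λg), with λ = -ln(0.05)/61.

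For a 1 May collection under the uniform delay, g runs from 1 to 61, so the mean share is 31/61 = 51%. In the last week of April g runs from 1 to 7, giving 4/61 = 7%.

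| Last collection | Uniform | Exponential |
|---|---|---|
| 1 May | 51% | 69% |
| 7 May | 60% | 77% |
| 1 June | 88% | 93% |
| 30 June | 100% | 98% |

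**5. Effect on the rate ratio.** Let f be the share of person-time in practices near the limit and c their captured share, with complete recording elsewhere and a complete baseline. Then observed ratio = true ratio × (1 - f + f × c). The true ratio is set to 2.0, as in the Section J simulation, and c to 0.51-0.75.

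| f | Observed ratio |
|---|---|
| 5% | 1.95-1.98 |
| 10% | 1.90-1.95 |
| 20% | 1.80-1.90 |
| 30% | 1.71-1.85 |

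For example, with f = 0.30 and c = 0.51: 2.0 × (0.70 + 0.153) = 1.71.

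**6. Against sampling error.** The Section J simulation gives 1.89 (1.74-2.07). Since 1.74/1.89 = 0.92 and 2.07/1.89 = 1.10, the interval extends about 8-10% either side. The loss is about 1-2% at f = 5% and about 7-15% at f = 30%. It therefore runs from well inside that interval to beyond it.

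**The case against.** The best defence is that the two-month delay was judged against builds. Section J says only that there appears to be one, and Section O measures it from the build. The figure may then already include the usual gap between collection and build. That is possible and would protect the average practice. It does not protect practices near the limit, which Section L expressly admits.

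The plan also has safeguards. Section O compares age- and sex-specific excess with national death registration data. Sections K and N plan a repeat with ONS death dates, and monthly updates will re-read March and April deaths from later builds. These have value, but the national comparison can reveal a shortfall without correcting it. The ONS repeat is secondary, depends on linkage coverage, and is restricted to England and linkage-eligible patients. Each monthly update moves the same weakness to the newest two months.

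A reader might infer more from the Section I table. In the April 2020 builds the row "February 2020 deaths" gives 2115/29 × 7 = 511 per week in GOLD, below the 2019 lower quartile of 537, and 6613/29 × 7 = 1596 in Aurum, below the median of 1657. This looks like direct proof of lost deaths, but it does not support the point. Applied to an early April build, the cut-off would fall at the end of January, so February lies in the period the plan discards. January, the last month kept, runs at 2747/31 × 7 = 620 in GOLD and 8318/31 × 7 = 1878 in Aurum, at or above the upper quartiles of 620 and 1845. The table also does not say that the Section L collection-date filter was applied. For the same reasons, a 10-15% loss over all of March and April, turning 2.0 into 1.7-1.8, cannot be derived from it.

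A reader might also infer that the subgroup interactions are necessarily biased. A common proportional loss cancels in those ratios. They are distorted only if completeness differs by characteristic, for instance because collection dates differ by region or database, and no section says that it does.

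**Conclusion.** The point holds as a flaw in the stated rule. Sections L and O use the same anchor, so eligibility secures coverage up to the study end but not the recording time that Section J says is needed. Practices last collected in May or June 2020 can contribute March and April person-time with incompletely recorded deaths, most severely those at the early-May limit. The direction is known: the overall pandemic effect is understated, with the baseline almost untouched.

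The size is not known. The range from 1.95-1.98 (5% of person-time) to 1.71-1.85 (30%) depends on the assumed delays, on deaths spread evenly over the window, and on the assumed share of practices near the limit. If few practices are near it, the effect is small.

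**What to change.** In Sections L and O, tie the allowance to the practice, by one of two routes:

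- End each practice's deaths and denominator together, two months before its own last collection date. A practice last collected on 1 May 2020 would then contribute to about 1 March.
- Keep the common end of 30 April 2020 and admit only practices last collected at least two months later, on or after about 30 June 2020. An early July build leaves a margin of only days, so the same end date may have to be run from a later build.

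Apply the chosen rule unchanged at each monthly update. Tabulating last collection dates by database and region would show how many practices are affected.

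The wording is short, but the change is not free. Some practices or recent weeks are lost, or the first result is later. Section J stresses the need for maximum data and reports 8% of cells with zero denominators in its simulation, so the loss should be counted before choosing. The ONS-linked repeat remains a useful later check, but a partial one.

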##### **2) Cohort approach**

The population under investigation will be the adult population contributing CPRD follow-up at any time after 1st March 2014.

#### **M. Selection of comparison group(s) or controls**

For the time series and SMR approach, the comparison is between observed aggregated mortality before and during the pandemic, investigated using respectively interaction terms with pandemic indicators, or comparisons with expected mortality modelled using pre-COVID-19 weekly aggregated data.

For the cohort approach, the comparison is between mortality during the pandemic period and mortality during the pre-pandemic period where information is kept at the individual-level (as opposed to aggregated).

[figure not shown]

#### **N. Exposures, Outcomes and Covariates**

The main exposure of interest is the Covid-19 pandemic starting from 1st March 2020.

The main outcome is mortality, identified from primary care data using the CPRD derived death date. In secondary analyses we will use updated linked ONS mortality data when available to repeat the analysis using the ONS death date.

Covariates of interest for stratification are:

- Geographical region
- Age (initial time series counts to be generated in 5 year categories, then collapsed further for analysis)
- Sex
- Smoking status (current, never, ex)
- BMI group (WHO groupings)
- Ethnicity (White, South Asian, Black, Mixed Other)
- Number of individuals in a household (CPRD GOLD only)
- Care home residency (CPRD GOLD only)
- History of comorbidities including those relevant to government “vulnerable groups” policy\*:
  - o Asthma
  - o Chronic respiratory disease (other than asthma)
  - o Cardiovascular disease
  - o Diabetes
  - o Cancer
  - o Chronic liver disease
  - o Chronic neurological diseases
  - o Chronic kidney disease
  - o Organ transplant recipients
  - o Problems with spleen
  - o On immunosuppressive drugs
  - o Hypertension
  - o Autoimmune disease
  - o Endocrine disease (including thyroid others)
  - o Multimorbidity

We will use code lists and definitions developed by the LSHTM Health Protection Research Unit on Immunisation where available, and where needed develop new code lists using systematic dictionary keyword searches, manual review, and clinical sign-off; these will be published online and linked in research outputs.

\*Current UK government guidance on who should be considered vulnerable has been largely based on policies developed for previous epidemic respiratory viruses, notably influenza. Understanding of Covid-19 risk factors is improving rapidly. We will submit a protocol amendment should new Covid-19 risk factors that can be measured using the available data emerge during the study.

[figure not shown]

## O. Data/ Statistical Analysis

To ensure our conclusions are robust, several approaches will be taken (with different strengths and limitations). We would expect the overall patterns and conclusions of the analyses to be similar. Any discrepancies in the patterns or results will be investigated and reported. In each case we will use data up to two months before the CPRD build date (i.e. data to end April 2020, from the build released in early July 2020) and analyses will be updated monthly.

### 1) Primary analysis - time series approach

We will derive weekly counts of numbers of deaths in contributing practices (see section L “Study Population”) from the start of the study period to the end of the study period. Population denominator sizes (number under active follow-up) will also be extracted. We will extract these counts overall, and stratified by age, sex, region and other factors (see section N “Covariates”). Where these factors are time-varying, counts will reflect changes over time.

We will fit generalised linear models with a negative binomial error structure to model the counts of deaths, taking account of variable denominator sizes [approach we took in Matthews et al media and statins paper to deal with variable denominators, BMJ2016]. The model will initially include the outcome (mortality), exposure (2020 pandemic period vs pre-pandemic), age, sex, interactions between the exposure and age and sex, Fourier terms (a harmonic function of calendar week) to capture seasonality, a continuous function of calendar year (linear, or higher order polynomial if evidence of non-linearity) to capture any underlying trends, and if relevant dummy indicators to capture extreme flu seasons. When investigating excess mortality within subgroups, further exposure covariate stratification factors will be added individually, and in combinations where there is sufficient information. Interactions between the exposure and stratification factors will provide estimates of the relative effect of the pandemic in strata.

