### *Specific aims (primary):*

1. Validate approaches/data by estimating all cause excess mortality, by age, sex and co-morbidity grouping, over time by week, during the COVID-19 pandemic in the UK, and compare with similar estimates derived from national death registration data.
2. Use time series methods to investigate how all-cause excess mortality varies by key individual-level characteristics (demographics, lifestyle-related, comorbidities).

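### The primary negative binomial model has no term for weekly shocks shared across strata or carried between weeks, so its intervals for overall excess mortality are too narrow wherever such variation remains

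*Protocol*

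**What the plan says.** Section O.1 derives weekly death counts and says "We will extract these counts overall, and stratified by age, sex, region and other factors". It then says "We will fit generalised linear models with a negative binomial error structure to model the counts of deaths", with variable denominators taken into account. The initial terms are a pandemic-period indicator, age, sex, their interactions with the period, "Fourier terms (a harmonic function of calendar week) to capture seasonality", a function of calendar year and "if relevant dummy indicators to capture extreme flu seasons".

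Primary aim 1 (section E) asks for excess mortality "over time by week, during the COVID-19 pandemic in the UK", and for comparison with estimates from national registration data. Primary aim 2 concerns variation by individual characteristics, which section O.1 estimates through interactions with the pandemic indicator.

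Section J reports one simulation on CPRD GOLD denominators: pandemic IRR 1.89 (1.74-2.07) and comorbidity interaction 1.97 (1.85-2.08), both with true value 2.0. Because both intervals contained the truth, it expects good coverage. It does not say whether the simulated data contained shared or autocorrelated weekly shocks. Section T names influenza and air pollution as outside influences on mortality, but nothing carries them into the variance.

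**The concern.** Influenza, weather and holidays move deaths in most age, sex and region cells in the same week, and often for several weeks. A negative binomial GLM gives each cell its own independent extra variation. When cells are summed over a week, that variation averages out in the model, but a shared shock does not. The model then treats about 322 correlated weeks, some 9 of them pandemic in the first analysis, as hundreds or thousands of independent observations.

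At stake are the interval for the overall pandemic IRR and, if taken from the same model, the weekly intervals under aim 1 and their comparison with national figures. Analyses are to be updated monthly, so weeks with small excess or deficit may enter. In those weeks the interval width decides how the result is read.

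**Working it through.** **The plan's own figures.** With SE = ln(upper/lower)/(2 × 1.96):
- Pandemic IRR: ln(2.07/1.74)/3.92 = 0.0443.
- Interaction: ln(2.08/1.85)/3.92 = 0.0299.

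Both intervals agree with their point estimates to rounding. The simulation cannot be rerun, because its strata, baseline rates and weekly noise are not given. One dataset whose intervals cover the truth does not establish coverage: if true coverage were 50%, a single interval would still cover half the time.

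**What the feasibility table shows.** Section I gives "Median (IQR) weekly deaths in 2019" as 560 (537-620) for GOLD and 1657 (1549-1845) for Aurum. With SD ≈ IQR/1.349:
- GOLD: 83/1.349 = 61.5, against Poisson √560 = 23.7. Variance ratio 6.8.
- Aurum: 296/1.349 = 219.4, against √1657 = 40.7. Variance ratio 29.

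This spread includes seasonality, which the Fourier terms are meant to remove. It is an upper guide to the residual shared variation, not an estimate of it.

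**Mechanism.** Let W be deaths per week, τ the SD of a shared residual shock on the log scale, and K the number of (equal) cells. The fitted dispersion is close to τ² per cell. The model's variance for a weekly log total is then about 1/W + τ²/K, while the true variance is 1/W + τ². With many cells the SE ratio for one week tends to √(1 + Wτ²):
- W = 560: τ = 3% gives √1.504 = 1.23; τ = 5% gives √2.400 = 1.55.
- W = 2,217 (560 + 1,657): τ = 3% gives √2.995 = 1.73; τ = 5% gives √6.543 = 2.56.

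For a nine-week mean with lag-1 correlation ρ = 0.6, τ² is multiplied by 1 + 2Σ(1 − k/9)0.6^k (k = 1 to 8) = 3.175. At W = 2,217 and τ = 3% the ratio is √(1 + 1.995 × 3.175) = 2.71. More pandemic weeks do not cure this: the factor rises towards (1 + 0.6)/(1 − 0.6) = 4. With K = 1 the two variances agree, so only autocorrelation remains.

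**Simulation.** 313 weeks before and 9 during the pandemic, true IRR 2, Fourier terms plus linear trend, dispersion by maximum likelihood. There were 100-400 runs per setting, so the Monte Carlo error of a ratio is up to about 7%. τ and ρ are assumptions. Entries are true SE / model SE for the overall pandemic log IRR, with 95% interval coverage in brackets.

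| Deaths/week, cells | τ 3%, ρ 0 | τ 3%, ρ 0.6 | τ 5%, ρ 0 | τ 5%, ρ 0.6 |
|---|---|---|---|---|
| 560, 120 cells | 1.35 (81.0%) | 2.03 (62.0%) | 1.91 (64.0%) | 2.78 (56.0%) |
| 2,217, 12 cells | 1.76 (73.5%) | 2.59 (50.5%) | 2.04 (70.5%) | 3.95 (38.5%) |
| 2,217, 120 cells | 2.09 (65.0%) | 3.32 (45.8%) | 2.81 (51.7%) | 5.28 (23.3%) |
| 560, one series | 1.01 (95.3%) | 1.44 (84.8%) | 1.03 (93.8%) | 1.57 (78.0%) |
| 2,217, one series | 1.08 (93.0%) | 1.74 (75.0%) | 1.03 (94.5%) | 1.76 (72.3%) |

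With no shared shock, the stratified ratio is 0.91-1.00 and coverage 95-97.5%. At τ = 8% and ρ = 0.6 it reaches 7.5 with 120 cells and 1.9 on one series, both at 2,217 a week. A separate simulation with 16 cells and τ of 3-5% gave 1.3-2.7 at 560 and 1.8-3.7 at 2,000 deaths a week.

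**Interactions.** Under a shock common to all strata, the interaction's SE ratio was 0.57-1.08 and coverage 92-100%, because the shock cancels. If shocks differ by stratum it does not fully cancel. With an assumed 3% without and 6% with the comorbidity (24 cells), the ratio was 1.5 (coverage 78%) at ρ = 0.6 and 1.2 (90%) at ρ = 0.

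**The case against.** The protocol nowhere states that cells are independent or that only model-based SEs will be used. It calls its list of terms initial, and robust errors or residual checks could sit in a statistical analysis plan that is not shown. That stands as far as it goes, and the absence of a stated autocorrelation check is not held against the plan. But the protocol does fix the error structure and then vouches for its coverage. Independence given the listed terms follows from that structure, and the coverage assurance is not supported.

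A reader might infer that the intervals are far too narrow as a matter of fact. The documents do not show this. Neither τ nor ρ is given, the 2019 spread includes season, and the influenza dummies may remove part of what is left. The figure of 2,217 is also on the high side: it sums two medians before practices in both databases are removed and before the restriction to continuous follow-up from March 2014. Fewer deaths lower the ratio.

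A reader might also infer that the aim 2 results are invalid. They are largely protected, as the interaction results show, unless shocks differ between strata. Nor is a large excess in doubt: at IRR 2, τ 3%, ρ 0.6 and 120 cells, the interval becomes 2 × exp(±1.96 × 0.0202) = 1.92-2.08, against 2 × exp(±1.96 × 0.0061) = 1.98-2.02.

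Finally, section O.1 gives no method for weekly intervals, so that part of the concern is conditional. The study is also descriptive and is checked against national data. Such a check can expose bias in the estimates, but it does not correct the width of the intervals.

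**Conclusion.** The point holds in a limited form. Fitted to week-by-stratum counts as written, the model gives intervals that are too narrow for the overall pandemic IRR, and for weekly excess if taken from it, whenever residual shared weekly variation remains. For an assumed 3-5% SD and ρ of 0-0.6, the true SE is about 1.35-2.8 times the model SE at 560 deaths a week and 1.8-5.3 times at 2,217, depending on the number of cells. On a single unstratified series only the autocorrelation part is left, about 1.4-1.8 times at ρ = 0.6. These multiples rest on assumed inputs; the direction rests on the model as written. The practical consequence is interval width and the reading of weeks with small excess or deficit. The coverage statement in section J is unsupported.

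**What to change.** For overall and weekly excess, do one of the following:

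- add a week-level random effect with AR(1) correlation to the stratified model; or
- fit the baseline to weeks before 1 March 2020 and form prediction intervals from its autocorrelated residuals.

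In either case, check residual autocorrelation and apply the method to placebo periods, 1 March-30 April of 2015 to 2019. Five placebo periods give only a coarse check, but one on the study's own data. Week-clustered robust errors alone are not enough with about 9 pandemic weeks. The interaction analyses can stay as planned, with a check on whether weekly residuals differ in size between strata.

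Withdraw the coverage statement in section J, or base it on many replicates that include shared, correlated weekly shocks.

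In one simulation on a single weekly series (8 pandemic weeks, ρ 0.6), an AR(1) error model raised coverage from 77.9% to 92.5% at 3% SD and from 72.6% to 93.2% at 5%. Those data were generated with AR(1) shocks, so this shows feasibility rather than performance on real data.

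The cost is wider intervals, some further analysis work and possible convergence effort in sparse strata. The changes section at the end of the protocol already reports convergence problems from low death counts. No new data are needed.
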